## Methods and analysis

This section outlines the methodological framework for the study, detailing the design, sampling, data collection instruments, and analysis strategies. The study uses a mixed-methods approach to collect both quantitative and qualitative data on public opinion regarding HHGE in South Africa. By integrating structured survey responses with open-ended qualitative input, the study aims to capture both measurable trends and nuanced perspectives. All procedures are designed to ensure ethical integrity, data quality, and demographic representativeness. This study has been granted institutional ethical clearance and will adhere to the principles of the Declaration of Helsinki.

### Study design

This study employs a cross-sectional survey design to measure spontaneous public opinion on various potential applications of HHGE among adult residents of South Africa. The survey is conducted online using SurveyMonkey and is structured around 19 scenarios derived from those used in the deliberative public engagement study by [name] et al. [9]. Of these scenarios, 15 correspond to [name] et al.’s [9] previous study, and there are five new scenarios that have been added or amended. Four of these scenarios relate to pandemic preparedness, a relevant topic given the recent COVID-19 pandemic. Furthermore, an additional new scenario, involving the creation of novel eye colours, has been included to explore public perceptions of genetic modifications beyond species-typical traits. These are explained further under the sub-section for ‘Survey instrument’. The inclusion of questions on both private morality (personal choice) and public morality (policy preference) provides a dual-lens analysis of ethical reasoning. Furthermore, participants will be asked to interpret the phrase ‘safe and effective’ to examine how their conceptual understanding shapes their views on the permissibility of HHGE applications.

### Participant recruitment and data collection processes

Participants will be recruited using targeted Facebook advertisements aimed at South African residents aged 18 years and older. Facebook was selected as the primary recruitment platform due to its extensive reach across demographic groups in South Africa. As of January 2024, approximately 74.7% of South Africans aged 16 to 65 reported using the internet, and of these individuals, 88.4% reported using Facebook at least once per month [10]. Therefore, 66% of the population within this age group likely use Facebook. This makes Facebook the social media platform with the highest advertisement reach in the country, rendering it both practical and cost-effective for large-scale recruitment.

Recruitment will occur in two phases. In the first phase, individuals will be directed via Facebook ads to the study’s dedicated Facebook page, where they can access a link to the screening questionnaire hosted on SurveyMonkey. Upon accessing the survey platform, potential participants will be presented with an informed consent form detailing the purpose of the study, data use, the voluntary nature of participation, and compensation procedures. Only those who consent on this online form via writing/ticking will proceed to complete the screening questions, collecting their demographic data, including age, sex, population group, educational attainment, and religious affiliation, along with an email address. These data will be used for stratified selection to ensure the final sample is demographically representative of the South African adult population.

In the second phase, 400 participants will be selected through stratified random sampling from the pool of respondents who completed the screening questionnaire. A stratified sampling approach will ensure that the final cohort of 400 participants reflects the demographic composition of the South African adult population. This design allows for comparison across population groups, age brackets, education levels, and other demographic variables. Selected individuals will be invited to participate in the full opinion survey via personalised email, containing a unique survey link. This approach prevents multiple completions and preserves the integrity of the dataset. Participants will be given two weeks to complete the survey. Reminder emails will be sent every two days until submission. If the response threshold is not met within the timeframe, a second batch of demographically matched participants will be invited, and this process will continue until 400 completed responses are obtained.

Participants who complete the full opinion survey will be fairly compensated their mobile phone number provided at the end of the survey. Only one response per cell phone number will be accepted, and participants providing duplicate entries will be excluded based on the criteria outlined below.

### Eligibility criteria

To be eligible to participate in the study, individuals must meet the following inclusion criteria:
Be a resident of South Africa.Be 18 years of age or older at the time of survey completion.Have access to the internet and be able to complete an online survey using a smartphone, computer, or similar device.Provide informed consent via the online forms to participate in the study, regardless of whether they are selected for the opinion survey phase.

For participation in the opinion survey phase specifically, selected individuals must also:
Complete all sections of the opinion survey.Provide a valid South African cell phone number to facilitate compensation.

Participants will be excluded from the study if they:
Do not meet the above inclusion criteria.Submit multiple responses using the same cell phone number – only the first complete response will be retained; subsequent entries from the same number will be excluded.Attempt to bypass the one-response rule by using different phone numbers, IP addresses, or browser profiles (measures such as IP tracking and browser restrictions will be enabled via SurveyMonkey to minimise this).Provide a non-South African cell phone number, indicating they are not residing in South Africa.Exhibit suspicious response patterns, such as unrealistically fast completion times or duplicative data entries.

These eligibility criteria are designed to ensure that the participant pool is both representative of the South African adult population and composed of genuine, engaged respondents.

### Sample size justification

The target sample size for this study is 400 participants. This figure was selected to achieve a balance between statistical robustness and practical feasibility. Given South Africa’s estimated adult population of approximately 46 million, a sample of 385 participants would typically be sufficient to ensure a 95% confidence level with a ±5% margin of error [11]. By increasing the sample size to 400, the study enhances the precision, reliability, and representativeness of its findings. This sample size also allows for meaningful subgroup analyses across key demographic variables, such as population group, age, sex, education level, and religious affiliation. Additionally, it supports the comparison between spontaneous public opinion and the informed deliberative views captured in previous studies by [name] et al. [9]. The sample size was chosen to accommodate potential variability in response patterns, ensure adequate statistical power for inferential tests, and reflect the diversity of South Africa’s adult population while maintaining an efficient, cost-effective research process.

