## Discussion

The prospective study based on this protocol offers a timely and necessary intervention into the emerging field of public engagement with HHGE, particularly within underrepresented contexts such as South Africa. By capturing the spontaneous, non-deliberative views of a demographically representative population sample, it responds to growing calls for more inclusive and locally grounded data on public attitudes toward genomic technologies.

For practice, the prospective study will provide empirical insights into how South Africans interpret core ethical concepts such as safety, effectiveness, and permissibility in the context of HHGE. These findings can assist clinicians, genetic counsellors, and science communicators in better understanding how laypeople perceive risk, choice, and therapeutic intention, enabling more responsive engagement and communication strategies in clinical and community settings.

For policy, the study will offer robust public opinion data that can inform governance frameworks for genome editing in South Africa. Unlike deliberative studies that rely on informed participants, this survey captures widespread public sentiment, including moral and cultural intuitions that may otherwise remain invisible in policymaking processes. The dual framing of private and public morality further enriches the data, offering insights into how individuals differentiate between personal autonomy and societal regulation. These perspectives are essential for ethical policy development, particularly in democratic societies seeking legitimacy through public consultation.

For scholarship, the study contributes to global literature by expanding the geographic and methodological scope of public opinion research on HHGE. It introduces an innovative comparative design that links deliberative and spontaneous viewpoints, and it pioneers the integration of generative AI tools in qualitative data analysis. This methodological contribution lays the groundwork for future research into the epistemological, ethical, and practical implications of AI-assisted qualitative methods in empirical bioethics.

Through its design and scope, the study supports a more inclusive, context-sensitive, and methodologically plural understanding of how emerging biotechnologies are received by the public, which is an essential step in fostering ethically sound and socially legitimate science policy.

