## Limitations

While the study is designed to maximise representativeness and rigour, several limitations must be acknowledged. There are three limitations that can be identified from the outset of the study: limitations in Facebook recruitment; the cross-sectional versus longitudinal nature of the study; and the use of GenAI in analyses.

First, the online nature of recruitment may exclude individuals without reliable internet access, particularly in rural or economically disadvantaged areas. This constitutes a limitation of the sampling approach. No supplementary recruitment strategies will be implemented beyond the online platform, and this limitation is acknowledged explicitly. Facebook advertising was selected as the primary recruitment method because it offers a cost-effective way to reach a national audience within the study’s resource constraints. Complementary recruitment strategies, particularly in rural areas, are not feasible due to the financial and logistical demands of travel, translation and gatekeeper permissions. We acknowledge that this may lead to under-representation of some groups and note this as a limitation and an avenue for future research. Nevertheless, recent national data suggest that as of January 2024, 66% of the population within the age group of 16 to 65 likely use Facebook [10]. While this figure may not capture all usage patterns, it suggests that Facebook provides extensive coverage of the general adult population, including a substantial proportion of users from diverse socioeconomic backgrounds. Given that the aim of this study is to explore public attitudes toward HHGE rather than to produce nationally representative estimates, recruitment through Facebook remains a reasonable and pragmatic approach.

Second, as a cross-sectional survey, the study captures views at a single point in time and does not account for how public attitudes may evolve through exposure to new information or public debate. The absence of a deliberative component means that changes in opinion arising from education, reflection, or dialogue are not measured within this study.

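### The ±5% margin behind n = 400 is not supported as a national margin by a weighted opt-in Facebook sample, and two unqualified claims of representativeness conflict with Limitations

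*Protocol article*

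**What the plan says.** The Sample size justification starts from a national population ("Given South Africa’s estimated adult population of approximately 46 million") and says that "a sample of 385 participants would typically be sufficient to ensure a 95% confidence level with a ±5% margin of error". The target is then set at 400, and by this increase "the study enhances the precision, reliability, and representativeness of its findings".

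The recruitment and sampling sections describe how the 400 are obtained. Facebook advertisements lead volunteers to a screening questionnaire. Stratified random selection is made from those who completed it. Non-responders are replaced within strata until 400 surveys are complete. Under Stratified sampling and randomisation, limited oversampling of minority groups is allowed, followed by weighting. On reach, the recruitment section says: "Therefore, 66% of the population within this age group likely use Facebook".

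The article describes the resulting sample in three ways:

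- **Demographic composition.** The recruitment section says "A stratified sampling approach will ensure that the final cohort of 400 participants reflects the demographic composition of the South African adult population", and the Discussion speaks of "By capturing the spontaneous, non-deliberative views of a demographically representative population sample". Stratified sampling and randomisation uses similar language.
- **Representative, without qualification.** The Abstract says that stratification will ensure a representative South African population. The Eligibility criteria say that the participant pool is representative of the country's adults.
- **Not nationally representative.** Limitations says: "Given that the aim of this study is to explore public attitudes toward HHGE rather than to produce nationally representative estimates".

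**The concern.** A margin of error is a property of a sampling design. The one quoted belongs to a design in which every adult in the target population has a known chance of selection and all responses count equally. This study has neither feature. Randomising within strata of a volunteer pool protects against bias in choosing among the volunteers. It does not correct for who uses Facebook, who clicks, who completes screening or who answers the invitation.

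The margin is the only numerical basis given for n. The Discussion also offers the results as input to governance of genome editing. A reader of the support percentages therefore needs to know which population they describe and which errors the stated precision leaves out. The article does not connect the margin to the sampling design, and its sections disagree on whether national representation is claimed.

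**Working it through.** **1. Reproduce the plan's figure.** Inputs from the Sample size justification: 95% confidence (z = 1.95996), margin e = 0.05, N of about 46 million. The proportion is not stated; p = 0.5 is assumed.

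n = z² × p(1 − p) / e² = 3.84146 × 0.25 / 0.0025 = 384.15, rounded up to 385.

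With the finite population correction, 384.15 / (1 + 383.15 / 46,000,000) = 384.14, again 385. The figure reproduces.

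**2. What the step from 385 to 400 does.** Margin = z × √(0.25 / n).

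- n = 385: ±4.99 points
- n = 400: ±4.90 points

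The gain is 0.09 points of sampling error. Coverage and self-selection do not depend on n, so representativeness is unchanged.

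**3. Effect of the planned weighting.** With design effect D, the margin at 400 is 4.90 × √D. It stays within ±5% only if D ≤ 400 / 384.15 = 1.04. The article gives no design effect, so the values below are assumptions.

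| Assumed D | Effective n (400 / D) | Margin at 400 | n for ±5% (384.15 × D) |
|---|---|---|---|
| 1.0 | 400 | ±4.9 | 385 |
| 1.2 | 333 | ±5.4 | 461 |
| 1.5 | 267 | ±6.0 | 577 |
| 2.0 | 200 | ±6.9 | 769 |

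**4. Coverage.** The recruitment section gives 74.7% internet use at ages 16 to 65 and, among those users, 88.4% on Facebook at least monthly. 0.747 × 0.884 = 0.660, so about 34% of that age band is outside the frame. People over 65 are eligible but are not in these figures.

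Suppose Facebook users and non-users differ in support by d points after stratification and weighting, and coverage is similar across strata. The bias is then about 0.34 × d. The document gives no value for d, so the range is assumed. The standard error is √(0.25 / 400) = 2.5 points, taking equal weights.

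| Assumed remaining difference d | Bias (points) | Actual coverage of a nominal 95% interval |
|---|---|---|
| 5 | 1.7 | about 90% |
| 10 | 3.4 | about 73% |
| 15 | 5.1 | about 47% |
| 20 | 6.8 | about 22% |

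This covers Facebook use only. Self-selection into the pool and non-response are further sources of error that the document gives no means to size.

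**5. Compare the claims.** Matching the sample's composition on age, sex, population group, education and religion is compatible with not aiming at national estimates. The unqualified statements in the Abstract and Eligibility criteria are not. Nor is a sample size justified by a margin on 46 million adults.

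**The case against.** The strongest reply is that the article is more careful than this suggests, and part of that stands.

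- Limitations names the exclusion of people without reliable internet access, possible under-representation in rural and poorer areas, and the lack of any supplementary recruitment, with reasons. The coverage limit is disclosed. What is missing is its link to the margin.
- Most statements on representation concern demographic composition. Stratification and weighting on five variables can largely deliver that. A reader might infer that every such statement contradicts Limitations. The text does not support this; the conflict lies with the Abstract and the Eligibility criteria.
- A reader might also infer that each support percentage will be published with ±5%. The article does not say so. The margin appears only as the reason for n, and Statistical analysis plans frequencies, chi-square tests and logistic regression.
- The biases above rest on assumed differences. Any difference between users and non-users that the five variables explain would be reduced by the planned adjustment. At a remaining difference of 5 points, the bias (1.7) is well below the margin (4.9). So it cannot be said that coverage error dominates, or that the precision is shown to be missed.
- The justification says typically, and a proportionate stratified probability sample would do about as well as a simple random one. The wording is hedged, but neither point describes a volunteer pool with unequal weights.

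**Conclusion.** The point holds, and the text is wrong as written. The calculation of 385 is correct, but the design does not support ±5% as a national margin. Two parts of this need no assumption about bias. First, any design effect above about 1.04 takes n = 400 past ±5%, and the plan includes oversampling with weighting. Second, the margin contains no coverage or self-selection error, and raising n cannot reduce it. The statement that going to 400 improves representativeness is incorrect.

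The margins of ±5.4 and ±6.0 rest on assumed design effects of 1.2 and 1.5. The size of any bias cannot be determined from the document, so the conclusion is that the stated precision is unsupported, not that a particular error will occur. Separately, the Abstract and the Eligibility criteria must be reconciled with Limitations.

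**What to change.** 1. In the Sample size justification, label ±5% (±4.9 at 400) as a nominal simple-random-sample figure, before weighting, coverage and self-selection. Beside it, give the margin under a stated design effect, for example ±5.4 to ±6.0 for 1.2 to 1.5.
2. Delete representativeness from the sentence on raising n from 385 to 400.
3. In the Abstract and the Eligibility criteria, replace the claim with a description such as: a non-probability sample of online adults, balanced on age, sex, population group, education and religion.
4. In the recruitment section, Stratified sampling and randomisation, and the Discussion, keep the claims to demographic composition only.
5. Report support percentages with design-weighted intervals, described as excluding coverage and self-selection error.

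The cost is wording and a weighted interval calculation. The stated precision becomes less favourable. The sample size and recruitment route stay as they are, and no extra participants are needed.

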### Stratified sampling and randomisation

A stratified sampling approach will be employed to achieve demographic representativeness of South Africa’s adult population. Stratification will be based on self-reported demographic characteristics collected during the screening phase, including age, sex, population group, education level, and religious affiliation (see Supplementary Materials for the full instrument). These strata reflect key sociodemographic variables used in national statistics and ensure that diverse population segments are proportionally represented in the final sample.

Within each stratum, participants will be randomly selected to reduce selection bias and maintain statistical rigour. Where minority demographic groups may otherwise be underrepresented, limited oversampling will be applied, followed by weighting adjustments during analysis to preserve overall representativeness. Replacement sampling will be conducted within strata to compensate for non-response until the target of 400 completed surveys is achieved. This stratified and randomised approach is designed to produce a sample that captures the heterogeneity of South African public opinion while balancing practical feasibility with methodological robustness.

### Pre-survey educational materials

To encourage participants to develop a basic understanding of key scientific concepts, respondents will be invited to view short, optional educational videos explaining the fundamentals of genetics and genome editing. The materials provide factual background on DNA, genes, and CRISPR-Cas9 without advancing any ethical positions that could bias participant responses. A full list of video titles and links is provided in the Supplementary Materials.

Although the educational materials were not formally tested for neutrality, they were reviewed by the multidisciplinary research team to ensure factual accuracy and non-evaluative content. Two videos provide simple, introductory explanations of genes and DNA, and the third – produced by the Mayo Clinic – describes how CRISPR works without presenting value-laden or speculative claims. These materials are included solely to provide a basic shared understanding, not to influence participant views.

The use of pre-survey educational content reflects the study’s commitment to transparency and comprehension while maintaining the non-deliberative nature of the data collection. Participants may proceed directly to the survey regardless of whether they view the materials, preserving the focus on spontaneous public attitudes that are typical of a democratic society. At the end of the questionnaire, participants will indicate whether they watched the videos, allowing for exploratory analysis of whether prior engagement with scientific information influences responses.

### Survey instrument

The survey instrument comprises two components: a demographic screening questionnaire and the main opinion survey assessing public views on HHGE. Optional open-text fields are included throughout to capture qualitative insights. Only respondents who complete the screening questionnaire and provide informed consent via the online form are considered for inclusion in the opinion survey. Collectively, the instrument is designed to elicit structured, comparative data while allowing for nuanced interpretation of underlying values through optional free-text responses.

The opinion survey (see Supplementary Materials) is organised into four sections:
**Interpretation of ‘safe and effective’** – examines how participants conceptualise safety in the context of HHGE by selecting among different definitions and, if desired, elaborating in an open-text response. To account for variability in how participants interpret ‘safe’ and ‘effective,’ the survey provides three predefined interpretive options for each term, based on widely accepted scientific and ethical understandings. Participants may also select ‘Other’ and provide their own explanation. These free-text responses will be reviewed to determine whether they align with the predefined categories or represent distinct interpretations. Patterns in ‘Other’ responses will be analysed to assess how public understandings converge or diverge from one another and from established scientific and health ethics definitions of safety and efficacy and public views on these matters [3].**Policy scenarios** – presents a range of possible HHGE applications, covering therapeutic, preventive, and enhancement purposes. Each scenario includes two decision contexts: a *private* decision (for one’s own hypothetical child) and a *public* decision (policy preference for society). This structure enables comparison between individual and collective moral reasoning.**General comments** – provides space for participants to express broader reflections on HHGE.**Media engagement** – records whether participants viewed the optional pre-survey educational videos or other media content related to genome editing.

The scenarios included in the survey were adapted from the structure and rationale of the original deliberative public engagement protocol by [name] et al. [8], which categorises applications of heritable genome editing (HHGE) into: (1) prevention of heritable genetic conditions; (2) editing for immunity; and (3) enhancement traits. This structure aligns with established international HHGE survey frameworks [7,12,13], thereby supporting comparability with global attitudinal data.

The prevention scenarios span a gradient of severity and are not context-specific, although examples are provided to guide participants’ understanding. Down’s syndrome and oculocutaneous albinism were included due to their prevalence in South Africa and the social stigma that these conditions often attract [14,15]. The editing-for-immunity scenarios follow the [name] et al. [8] framework and incorporate conditions of particular relevance to South Africa’s disease burden. In 2022, TB was the second leading cause of death by a single infectious agent, with one of the highest incidence rates globally (more than 10 million per year) [16]. Statistics for 2024 show that South Africa 389 people per 100,000 contracted TB, whilst it caused approximately 54,000 deaths. More than half these deaths were in people co-infected with HIV [17], an infection that affects approximately 8 million South Africans [18]. The combination of high prevalence, co-infection patterns, and associated mortality creates an epidemiological context in which editing-for-immunity represents a salient and meaningful category for public opinion research.

The original COVID-19 immunity scenario from [name] et al. [9] was adapted into a broader pandemic-causing disease scenario, comprising four questions. Although HIV/AIDS and TB have been epidemics in the South African context [19], these four scenarios are more hypothetical and directed towards a transnational event, such as COVID-19, which now exists in the global collective memory. These scenarios can be split according to the severity of the hypothetical pandemic and to the availability of a vaccine that confers immunity. These questions have been included to explore public opinion on using HHGE to prepare for future pandemics. This approach acknowledges COVID-19 as a recent global pandemic while also allowing respondents to consider future outbreaks where vaccines may or may not be available. Given the controversy surrounding the speed of COVID-19 vaccine development [20], the scenario provides an opportunity to assess whether HHGE is perceived as a viable alternative in the context of public health emergencies.

The enhancement scenarios – covering traits such as intelligence, athleticism, aggressiveness, cooperativeness, sexual orientation, skin tone, and eye colour – mirror both the original [name] et al. [8] framework and widely used categories in international surveys [7,12,13]. These traits highlight ethical questions related to parental choice, fairness, and social norms. Certain traits (e.g. skin tone) also carry specific sociocultural resonance within South Africa’s historical context, supporting their inclusion as distinct scenarios. Furthermore, to the last theme of scenarios, that is, editing for enhancement, an additional new scenario, involving the creation of novel eye colours, has been included to explore public perceptions of genetic modifications beyond species-typical traits.

The survey instrument was adapted from a previously validated questionnaire developed for an earlier study on deliberative public engagement, conducted by the same principal investigator [8,9]. In that study, the instrument underwent extensive piloting to assess clarity, comprehension, and cultural appropriateness for South African participants. The current version retains the core items from the validated instrument, with only minor contextual adaptations to align with the present study’s focus.

Given this prior piloting and validation, re-piloting the instrument was deemed unnecessary and ethically inappropriate, as it would involve re-exposing participants to nearly identical sensitive material. Instead, internal review and content validation were undertaken within the research team to ensure that all modifications preserve conceptual integrity, linguistic clarity, and cultural relevance.

